### Follow up

We will assess outcomes at 6 months (at the end of the control period), 12 months (at the end of the cafeteria intervention), and 18 months (at the end of the behavioral intervention). During each follow up, fasting blood samples will be collected and analyzed for HbA1c, fasting glucose, and lipid profile (HDL, LDL, total cholesterol, triglycerides). We will re-administer the global physical activity questionnaire, and the two 24-h diet recalls. We will re-measure height, weight, waist circumference, and blood pressure at each of these time points as well.

### Primary and secondary outcomes

The primary outcome will be the proportion of individuals reaching two or more of their cardio-metabolic risk goals, reductions in blood pressure, triglycerides, and HbA1c. Participants will be scored on the number of improved risk factors (0–3) as defined by decreases in (1) HbA1c ≥0.5%; (2) systolic blood pressure ≥ 5 mmHg; or (3) plasma triglycerides ≥10 mg/dl. These outcomes were selected because blood pressure, HbA1c, and triglycerides are commonly measured in clinical settings. This makes their use clinically appropriate and translatable, especially since other CVD risk scores such as the Framingham Risk Score, do not perform well in South Asian populations [25]. Moreover, the composite outcome allows for individuals to reduce different factors based on their variable risk profiles at baseline. For example, an individual with a baseline systolic blood pressure of 120 mmHg many not reduce this risk factor by as much as 5 mmHg, but may succeed in reducing HbA1c or triglycerides. The secondary outcomes are absolute changes in HbA1c, systolic blood pressure, diastolic blood pressure, and triglycerides individually.

### Data management

We have taken four robust provisions to ensure data quality. First, the electronic questionnaire will be closed only if the data collection is complete to avoid partial or missing values. The data will be cleaned and checked every month. The answer fields for all integer variables will be constrained to ensure entry of only valid numbers. Second, RAs will receive intensive training on data collection and ethical considerations. Third, the site investigator will supervise the RAs on a day-to-day basis. Fourth, the principal investigators will hold weekly meetings with site investigators, and if required, with the RAs, to discuss the course of the intervention and to address any issues.

#### Data analysis plan

The primary analysis will be intention to treat. The quantitative data analysis will follow the Consolidated Standards of Reporting Trials (CONSORT) guidelines [26]. The flowchart will include the number of participants seen at each stage, including the number screened, eligible, randomized, and analyzed for the primary outcomes.

#### Effectiveness of the cafeteria intervention

At the 12-month follow-up, we will compare the proportion of participants who achieved two or more of their cardio-metabolic risk factor reduction goals during the cafeteria intervention period, to the proportion of participants in the control period, using the generalized estimating equations (GEE) approach with the binary distribution, logit link function and an exchangeable working correlation structure [27].

#### Effectiveness of the behavioral intervention

At the 18-month follow-up, we will compare the proportion of participants who have achieved two or more of their cardio-metabolic risk factor reduction goals in CO arm to the proportion of participants in the CB arm using a *χ*^2^ test. In the event that randomization does not appear to have controlled for differences between the treatment and control groups on baseline characteristics, in secondary analysis, we will statistically control for those differences using the GEE approach with the binary distribution, logit link function and an exchangeable working correlation structure [27].

Our secondary analysis will compare the change in HbA1c, systolic blood pressure, and lipids during the cafeteria-only intervention to the change during the control period using a paired t-test. Similarly, we will compare the change in HbA1c, systolic blood pressure, and lipids between CO group and CB group using a paired t-test. Assumptions of the statistical tests will be examined and if violated non-parametric testing will be explored. In the event that randomization does not appear to have controlled for differences between the treatment and control groups in baseline characteristics, we will conduct the GEE approach with the Gaussian distribution, identity link function and an exchangeable working correlation matrix [27] to adjust for potential confounding factors. The data will be analyzed using STATA-15.

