### Data collection

The schedule of enrollment and assessment is presented in Table 1. At baseline, we will measure demographics, anthropometry, blood pressure, lifestyle, blood sugar and lipid profile. After 6 months of control period (without any intervention), we will measure the anthropometry, lifestyle, blood sugar and lipid profile. We will implement the cafeteria intervention for 6 months and re-measure the anthropometry, lifestyle, blood sugar and lipid profile at 12 months. Then, we will randomize half of the participants to continue the cafeteria intervention in addition to a behavioral intervention for the prevention of cardio-metabolic risk, while the other half of participants will receive the cafeteria-only intervention. We measure the anthropometry, lifestyle, blood sugar and lipid profile at 18 months.

**Table 1 Tab1:** The schedule of enrollment and assessments for the Nepal Pioneer Worksite Intervention Trial

	Screening Month 1	Baseline Month 1–2	Follow up - 1 Month 6	Follow up- 2 Month 12	Follow up- 3 Month 18
Indian Diabetes risk score questions (age, sex, family history of diabetes self-report moderate physical activity)	X				
Demographic information (age, sex, ethnicity, education, income, religion, marital status)		X			
Anthropometry					
Height		X			
Weight		X	X	X	X
Waist circumference	X	X	X	X	X
Hip circumference		X	X	X	X
Blood Pressure	X	X	X	X	X
Lifestyle factors					
Two 24 Hour Dietary recall		X	X	X	X
Global physical activity questionnaire		X	X	X	X
Smoking and Drinking habits		X		X	
Laboratory					
Glycated hemoglobin	X	X	X	X	X
Fasting Blood Sugar	X	X	X	X	X
High density lipoprotein cholesterol		X	X	X	X
Low density lipoprotein cholesterol		X	X	X	X
Triglycerides		X	X	X	X
Total Cholesterol		X	X	X	X

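### Randomised phase: covariates enter only if an imbalance appears, so the adjusted secondary models are chosen from the data and modest precision from the month-12 values is forgone

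*Protocol article*

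**What the plan says.** The section on effectiveness of the behavioral intervention sets the 18-month test of the composite as a comparison of the proportion "in CO arm to the proportion of participants in the CB arm using a" chi-square test, with no covariates. Adjustment is conditional: "In the event that randomization does not appear to have controlled for differences between the treatment and control groups on baseline characteristics", then "in secondary analysis, we will statistically control for those differences using the GEE approach".

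The next paragraph, on secondary outcomes, compares changes between arms with a t-test and repeats the condition: "In the event that randomization does not appear to have controlled for differences between the treatment and control groups in baseline characteristics", in which case "we will conduct the GEE approach with the Gaussian distribution, identity link function and an exchangeable working correlation matrix".

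The composite counts improved risk factors, "as defined by decreases in (1) HbA1c ≥0.5%; (2) systolic blood pressure ≥ 5 mmHg; or (3) plasma triglycerides ≥10 mg/dl", and success is two or more. The section on outcomes accepts that the starting value matters: "an individual with a baseline systolic blood pressure of 120 mmHg many not reduce this risk factor by as much as 5 mmHg".

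The section on data collection places randomisation after the month-12 measurements. Its Table 1 ("The schedule of enrollment and assessments for the Nepal Pioneer Worksite Intervention Trial") schedules HbA1c, blood pressure and triglycerides at month 12 for every participant. The column headed baseline in that table is month 1–2. The analysis section does not say whether its baseline characteristics are those of month 1–2 or of month 12, nor from which visit the 18-month decrease is counted.

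**The concern.** Arms formed by computer-generated random numbers differ at the start only by chance. Asking whether randomisation has worked therefore tests nothing, and covariates picked because they happen to differ need not predict the outcome. Whether an adjusted model is run, and which variables it holds, is then settled after the data have been seen.

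The covariates with a clear prior claim are known now: the last pre-randomisation values of the three markers that make up the outcome. A participant who is high by chance at month 12 tends to fall by month 18, and one who is low tends not to. Adjusting for those values removes that noise. Under the plan as written they may never enter a model if the arms look alike, or if baseline is read as month 1–2.

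At stake are the credibility of the adjusted secondary results and some precision that costs no further data.

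**Working it through.** **The plan's own power figure.** Inputs from the section on sample size and power: 320 participants, 5% loss, control proportion 0.315, relative risk 1.5, 5% level (taken as two-sided). This gives 0.315 × 1.5 = 0.4725 in the other arm and 160 × 0.95 = 152 per arm. The pooled proportion is 0.39375.

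- Null SD term: √(2 × 0.39375 × 0.60625) = 0.691
- Alternative SD term: √(0.315 × 0.685 + 0.4725 × 0.5275) = 0.682
- z = (0.1575 × √152 − 1.96 × 0.691) / 0.682 = 0.862, so power = 0.806

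The stated 80% reproduces. The requirement is 150 per arm, or 316 in total after 5% loss, against 320 planned.

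**Continuous markers.** Table 3 gives an SD of 13.32 mmHg for systolic pressure, taken from baseline values. The detectable difference for independent samples is 2.80 × 13.32 × √(2/152) = 4.28, which matches the printed 4.3.

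Let r be the month-12 to month-18 correlation of a marker, with equal SDs. A change score has SD 13.32 × √(2(1−r)); ANCOVA on the month-12 value has residual SD 13.32 × √(1−r²). The variance ratio is (1−r²) / (2(1−r)) = (1+r)/2. The article does not give r. Its values of 0.5 to 0.7 belong to the before-after design, where the Table 3 footnote defines them as correlations between changes. So r is an assumption here, taken over 0.5 to 0.9.

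| r | change score, mmHg | ANCOVA, mmHg | variance ratio |
|---|---|---|---|
| 0.5 | 4.28 | 3.71 | 0.75 |
| 0.7 | 3.32 | 3.06 | 0.85 |
| 0.9 | 1.91 | 1.87 | 0.95 |

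A ratio of 0.75 is worth 1/0.75 = 1.33 times the participants; 0.95 is worth about 1.05 times.

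**Composite.** Trials were simulated with 152 per arm, the Table 3 SDs, the protocol's thresholds, normal and mutually independent markers, and success rates calibrated to 31.5% and 47.25%. There were 4,000 trials per setting for power and 2,000 for type I error. Because the reference visit is not stated, both readings were run. With change from month 12, the logistic model held the three month-12 values. With change from the first visit, it held the first-visit and month-12 values.

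| Change from | r | chi-square power | adjusted power | variance of outcome explained | AUC |
|---|---|---|---|---|---|
| month 12 | 0.5 | 0.818 | 0.861 | 10.5% | 0.70 |
| month 12 | 0.7 | 0.804 | 0.820 | 6.4% | 0.65 |
| month 12 | 0.9 | 0.807 | 0.807 | 2.3% | 0.59 |
| first visit | 0.5 | 0.811 | 0.854 | 14.5% | 0.73 |
| first visit | 0.7 | 0.822 | 0.863 | 12.9% | 0.72 |
| first visit | 0.9 | 0.806 | 0.848 | 12.3% | 0.71 |

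A separate run of 2,000 trials per setting, with change from month 12, gave 0.801 to 0.850 at r = 0.5 and 0.797 to 0.804 at r = 0.9. Across both runs the gain is about 0 to 5 points. Simulated type I error was 0.048 to 0.057 over both tests.

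**The case against.** The strongest reply is that the primary result is fixed. The chi-square is unconditional, it is valid under randomisation, and it has the power claimed for it. Both conditional adjustments are secondary. This stands: a reader might infer that the primary p-value can be chosen after the data are seen, and the text does not support that.

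Nor does it support the inference that the plan throws away values that largely settle the outcome. If change is counted from month 12, those values already enter through the change; only their use as covariates is lost. In simulation they explain about 2% to 11% of the variance of the composite, so they are prognostic and no more.

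It might also seem that a GEE with exchangeable correlation is an error where each participant has one 18-month outcome. It does no harm: with one record per person it reduces to an ordinary regression with robust standard errors.

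The size of the gain depends on a correlation that the article does not supply. The 4.3 to 3.7 mmHg figure is the most favourable of the values tried, and the benefit shrinks as r rises. This also stands, which is why the range is shown.

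Finally, an imbalance criterion and a covariate list may sit in an analysis plan that is not at hand, so their absence is not held against the article. But the conditional rule is itself stated here, twice, and a criterion added elsewhere would still select covariates by observed difference.

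**Conclusion.** The point holds as a modest, low-cost improvement. The article makes adjustment in the randomised phase depend on an apparent imbalance, which is a poor rule for choosing covariates, and so gives no assured role to the month-12 markers.

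The consequences are a data-driven choice of secondary model and some lost efficiency: about 0 to 5 points of power for the composite, and for systolic pressure a detectable difference larger by 0.6 mmHg at r = 0.5, by about 0.3 at r = 0.7 and by less than 0.1 at r = 0.9. There is no bias, no inflation of the primary test's type I error and no shortfall against the stated power. The sizes rest on the assumed correlations, independent normal markers (a simplification for triglycerides) and equal SDs at the two visits.

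**What to change.** - Delete both conditions on apparent imbalance.
- State that the 18-month change is counted from month 12, the last visit before randomisation, if that is what is intended. If the first visit is meant, say so and add its values to the covariates.
- For each continuous marker, prespecify ANCOVA of the 18-month value on arm and the month-12 value, whatever the observed balance.
- For the composite, prespecify a logistic model with arm and month-12 systolic pressure, HbA1c and triglycerides. Report it as a marginal risk ratio and risk difference, which keeps the relative-risk scale of the sample size section. Show it beside the chi-square, which may remain the primary test.

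The cost is a change of wording to the secondary analyses. Table 1 already schedules every value needed. With the chi-square kept as primary, neither the primary test nor the sample size changes.

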## Methods

### Study design

The Nepal Pioneer Worksite Intervention Study is a two stage intervention study. In the first stage, we will use a pre-post design to assess how a cafeteria intervention that provides a healthier diet, affects cardio-metabolic risk. In the second step, we will conduct an unmasked two-arm randomized trial by allocating half of the participants to continue the cafeteria intervention in addition to a behavioral (CB) intervention for the prevention of cardio-metabolic risk, while the other half of participants will receive the cafeteria-only (CO) intervention. (Fig. 1) The study protocol has been approved by the institutional review committee at Harvard T.H. Chan School of Public Health, Nepal Health Research Council, and Kathmandu University School of Medical Sciences. The study has been retrospectively registered in clinicaltrials.gov (Identification Member: NCT03447340) on February 27, 2018.

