#### Step 2: The behavioral intervention

After 6 months of the cafeteria intervention, half of the participants will be randomized using computer generated random numbers to receive a cafeteria and behavioral intervention (CB), the other half of the participants will continue to receive the cafeteria only (CO) intervention. The behavioral intervention will be comprised of intensive education sessions, group counseling, and goal setting and monitoring exercises based on the Diabetes Prevention Program (DPP) [24] tailored to local needs. The curriculum includes 24 sessions of 16 core weekly sessions during the first 4 months of this phase of the intervention followed by 8 weekly maintenance sessions. Each session will be 1 h long, and will be facilitated by a dietitian. Broadly, the curriculum covers subject matters of importance for achieving and maintaining healthy weight, eating a healthy diet, increasing physical activity, stress management, and overcoming common challenges encountered when making lifestyle changes. Similar to the cafeteria intervention, healthy eating messages include increasing fresh fruits and vegetable intake, avoiding added sugar, choosing whole grains, choosing healthier sources of protein, reducing sodium, and monitoring portion sizes. Participants will be encouraged to keep food and activity diaries throughout the course of the study. The maintenance period’s focus will be on overcoming declines in motivation and maintaining long-term healthy behaviors. All of the sessions will be conducted at the worksite during the workday. There will be about 20 participants in each education class. Participants will set a minimum of two lifestyle-change goals (e.g. Half of their total grain intake will be whole grains, walking 30 min a day, or reducing 7% of their body weight).

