### Sample size and power

The pre-post design, with at least 366 eligible and enrolled participants [28] and 5% loss to follow-up (LTF) after 12 months, will have over 90% of power to detect the primary effectiveness endpoint of this trial, of 31.5% or greater, compared to the 21% change in the control group seem previously in a South Asian population [29]. For the analysis of two randomized groups (CO and CB arms), with 320 participants, we will be able to detect a relative risk of 1.5 given 0.315 risk probability in the control group, 5% LTF rate with 80% power and 5% level of significance [30].

In the secondary analysis, where we will compare the within-participant changes in HbA1c, systolic and diastolic blood pressure, and lipids observed in the cafeteria intervention to those observed in the behavioral intervention. Given the sample sizes of 366 and 320 respectively, 5% LTF rate with 80% power and 5% level of significance, we will be able to detect the minimum differences as presented in Table 3. For the before-after design, we considered three possible values of the correlation (*ρ* = 0.5, 0.6, 0.7) between repeated measurements during the control period and during the intervention period.

**Table 3 Tab3:** Minimum absolute detectable differences for the change in glycosylated hemoglobin, systolic and diastolic blood pressure, and triglyceride for sample sizes of 366 and 320 correspondingly, 5% loss-to-follow-up rate with 80% power and 5% level of significance, for the Nepal Pioneer Worksite Intervention Trial

		Minimum absolute detectable difference			
		*N* = 366			*N* = 320
Parameter	Std. Dev.	*ρ*^∗^=0.5	*ρ*^∗^=0.6	*ρ*^∗^=0.7	Independent samples
Glycated hemoglobin, %	0.38	0.06	0.05	0.045	0.12
Diastolic blood pressure, mmHg	9.43	1.4	1.3	1.1	3
Systolic blood pressure, mmHg	13.32	2	1.8	1.6	4.3
Triglycerides, mg/dL	82.47	12.5	11.2	9.7	26.6

*Correlation between the changes of the same individual observed during control and treatment periods of time

Standard deviations are calculated from the baseline data of the study participants

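### The CO versus CB comparison of changes is assigned a paired t-test, but the arms contain different people and no pairs exist

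*Protocol article*

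**What the plan says.** Under 'Effectiveness of the behavioral intervention', the Protocol article gives two secondary comparisons of continuous outcomes in consecutive sentences.

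- The first compares each person's change "during the cafeteria-only intervention to the change during the control period using a paired t-test". Both changes come from the same person, so pairing is right there.
- The second is introduced as similar and reads: "we will compare the change in HbA1c, systolic blood pressure, and lipids between CO group and CB group using a paired t-test".

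The arms are described under 'Step 2: The behavioral intervention': "half of the participants will be randomized using computer generated random numbers" to the CB arm, and "the other half of the participants will continue to receive the cafeteria only (CO) intervention". 'Study design' calls this an "unmasked two-arm randomized trial by allocating half of the participants". Matching, pairing or pair identifiers across arms are not mentioned anywhere.

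'Sample size and power' treats the arms as "For the analysis of two randomized groups (CO and CB arms), with 320 participants", and Table 3 heads the N = 320 column "Independent samples". The within-person correlations of 0.5, 0.6 and 0.7 are used only for the before-after design.

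**The concern.** A paired t-test analyses one difference per pair, so every CO participant would need a designated CB partner. Individual, unmatched randomisation does not create partners.

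An analyst who follows the sentence has two ways to make it run, and neither is acceptable:

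- **Pair by row.** Participants are paired by their position in the file. The p-value then depends on sort order, and if the arms finish with unequal numbers the surplus participants cannot be used.
- **Pair within arm.** Month 12 is compared with month 18 separately in CO and in CB. Those are valid paired tests, but they do not compare the arms, and the benefit of randomisation is lost.

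The randomised phase is the only part of the study with a concurrent control, so the test named for its continuous outcomes should be one that can be carried out.

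**Working it through.** **Inputs** (all from 'Sample size and power' and Table 3): 320 participants in two equal arms, 160 each; 5% loss to follow-up, leaving 160 × 0.95 = 152 per arm; 80% power; 5% significance level. Sidedness is not stated; two-sided is assumed, and it reproduces the table. SDs: HbA1c 0.38, diastolic pressure 9.43, systolic pressure 13.32, triglycerides 82.47.

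**Step 1. Reproduce the N = 320 column as two independent samples.**

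Detectable difference = (1.960 + 0.842) × SD × √(2/152) = 2.802 × SD × 0.1147

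| Outcome | SD | Computed | Table 3 |
|---|---|---|---|
| HbA1c, % | 0.38 | 0.122 | 0.12 |
| Diastolic BP, mmHg | 9.43 | 3.03 | 3 |
| Systolic BP, mmHg | 13.32 | 4.28 | 4.3 |
| Triglycerides, mg/dL | 82.47 | 26.5 | 26.6 |

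Power at the printed differences is 78.6%, 79.2%, 80.4% and 80.3% respectively. The column is an unpaired calculation.

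**Step 2. Confirm that pairing was assumed only for the before-after design.**

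Detectable difference = 2.802 × SD × √(2(1 − ρ)) / √n

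- Systolic pressure with n = 366 × 0.95 = 347.7 and ρ = 0.5, 0.6, 0.7: 2.00, 1.79 and 1.55, against the printed 2, 1.8 and 1.6.
- The same formula with 152 genuine CO–CB pairs would give 3.03, 2.71 and 2.34, not 4.3.

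So Table 3 did not assume pairs between arms.

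**Step 3. What arbitrary pairing does to one data set.** With equal arms and equal SDs, t(paired) = t(two-sample) / √(1 − r), where r is the chance correlation produced by the row order. Over random orderings r has mean 0 and SD 1/√151 = 0.081, so 95% of orderings give r within about ±0.16.

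Take a two-sample p of 0.035 (t = 2.118 on 302 df):

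- r = +0.16: t = 2.118 × 1.091 = 2.31 on 151 df, p = 0.022
- r = −0.16: t = 2.118 × 0.929 = 1.97 on 151 df, p = 0.051

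Simulation agrees. With 152 per arm, SD 13.32 and data sets chosen to have a two-sample p of 0.02 to 0.05 (mean 0.035), re-pairing moved p over about 0.023 to 0.051. In separate runs, roughly 7%, 10% and 11% of orderings crossed 0.05.

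**Step 4. Long-run behaviour without selecting borderline data.** In 20,000 simulated trials with 152 per arm:

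| | Arbitrary pairing | Two-sample |
|---|---|---|
| Type I error | 5.3% | 5.2% |
| Power at the Table 3 difference | 79.4% | 79.8% |

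In further unselected runs the two tests disagreed on significance in about 0.7 to 0.8% of data sets under no effect, and in 1.7 to 2% at the Table 3 systolic difference. All these runs assume equal arms; unequal arms would also lose data.

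**The case against.** The strongest reply is that this is a slip of one word. The paired test was probably carried over from the preceding sentence, Table 3 shows what was meant, and an analyst with no pair identifier would notice that the test cannot be run. Only secondary outcomes are touched: the primary CO versus CB comparison is a chi-square test, and the primary cafeteria analysis is a GEE model. Average error rates barely move, and the 7 to 11% crossing rate applies only to borderline data sets.

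Most of this stands as a limit on size and scope. The sentence names HbA1c, systolic pressure and lipids. Diastolic pressure, also a secondary outcome, is not mentioned in it. The harm is not an inflated type I error or a wrong sample size.

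It does not rescue the text. The paired test is stated outright as the default for these outcomes, so this is not a detail left out of a condensed article. The two alternatives in the same section are conditional: non-parametric testing applies if assumptions are violated, and the Gaussian GEE applies if baseline imbalance appears. Neither replaces the default test.

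It is also fair to say that correcting the error strictly requires only an unpaired test. Baseline-adjusted regression is a preference for precision.

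**Conclusion.** The concern holds. The stated test cannot validly be applied to CO versus CB, and it contradicts the independent-samples basis of Table 3, which reproduces to within rounding or about 0.1 in every row.

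The numerical effect is modest: type I error near 5% and power near 80% under either test, with different significance calls in about 1 to 2% of data sets. The correction is needed because the prespecified analysis is undefined and depends on file order. It covers the continuous secondary outcomes of the randomised phase that the sentence names. The primary comparison and the sample size are not affected.

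The figures assume a two-sided 5% level, 152 analysed per arm, normally distributed data and equal SDs.

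**What to change.** Replace the paired t-test for CO versus CB with a between-arm analysis:

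- **Minimum:** a two-sample (Welch) t-test on the change from month 12 to month 18. This keeps the stated difference in change and agrees with Table 3.
- **Preferable:** a linear regression (ANCOVA) of the 18-month value on arm and the participant's month-12 value, which is already collected. It normally gives better precision.

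Name diastolic pressure in the same sentence, since it is a listed secondary outcome and Table 3 powers it. Keep the paired t-test for the cafeteria-period versus control-period comparison only.

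The cost is one sentence in the analysis plan. No extra data are needed and no sample-size figure changes.
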